### 5.9 Visit 6- (within 2 weeks of visit 5) In-depth Telephone Interview

Study staff will contact subject to conduct in-depth acceptability interview via telephone (see script in Appendix VI). Interviewers will use a basic script to initiate discussion, but interviews will vary according to participant responses.

## 6.0 SAFETY MONITORING AND ADVERSE EVENT REPORTING

### 6.1 Safety Monitoring

The study site Investigators are responsible for continuous close safety monitoring of all study participants, and for alerting the protocol team if unexpected concerns arise. The protocol team will meet via conference call every two to four weeks during the period of study implementation, and additional ad hoc calls will be convened, if required. A decision to convene the SMC may be made at any time that the team agrees that an unacceptable type and/or frequency of AEs has been observed.

In addition, accrual will be suspended and the UCLA SMC will be convened, if **two or more** study participants experience an **AE  $\geq$  Grade 3**. If the SMC feels the AE's may be sufficient to halt the trial, the SMC will be unblinded. The SMC will then analyze the data in an unblinded fashion and make the determination on whether to continue accrual and product use. No other study staff will be unblinded until the study has been terminated and the data locked down.

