## 2.2 Study Design

This is a phase I randomized, blinded, placebo-controlled study of the safety and acceptability of the vaginal formulation of UC-781 gel, when administered rectally, to be conducted in 36 adults (12 per group) residing in the Los Angeles, CA area. All of the participants will be HIV negative. The study design is summarized in the Schema above and the Schedule of Events in Appendix I.

This study will involve 2 stages of treatment. Each treatment stage is independent of the other. **This study aims to examine the effects of 2 different dosing regimens, NOT cumulative toxicity over both stages.** Participants will undergo extensive evaluation during 5 study visits over an approximately 7-14 week period. In addition, acceptability assessments will be completed at baseline and Visit 5.

Interested participants will enter a screening period, which includes (Visit 1) and if necessary a medication washout period. Subjects, who are deemed eligible after this screening period, will return for a baseline evaluation (Visit 2), including clinical evaluation and mucosal specimen collection, as well as a baseline behavioral assessment (BBQ). The BBQ questionnaire will be administered by CASI. Subjects may complete the web-based CASI in the privacy of their own home. If a subject does not have access to the internet, prefers to complete the BBQ at the study site, or requires assistance in using the CASI, they will be accommodated at the study site.

After completing Visits 1 and 2, eligible subjects will be randomized to one of three groups: 0.1% UC-781 gel, 0.25% UC-781 gel, or a placebo gel (12 per group). A subset of 9 subjects (3 from each group) will also participate in a pK sub-study, which will include 6 timepoints (Visit 3- pre, 0.25 hr, 2 hr, 4 hr, Visit 3A- 24 hr, and Visit 5- 1 day post-QD dose draw). During randomization, study staff will be notified if the participant is randomized to the pK sub-study. Subjects will be randomized in blocks of 3, one per group to minimize imbalance in treatment assignments. The first three subjects enrolled in each of three treatment groups will be selected for the pK sub-study. It is possible that participants may refuse to participate in the sub-study, and spots will continue to be offered as needed.

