## 5.3 Visit 3- (Week 2 +/- 1 week) Single Dose Administration

### 5.3.1 Non-clinical Procedures

- ⊙ Randomize subject and assign participant ID number prior to Visit Day
- ⊙ Provide test results from Visit 2 and post-test counseling.
 

*If any lab abnormalities ≥Grade 2, subject may not proceed with Visit 3. If the investigator feels that the laboratory abnormalities are transient, the lab tests may be repeated within the visit window. If the repeated labs tests are within normal limits, the subject may proceed with Visit 3 at the discretion of the investigator, the DAIDS Medical Officer, the SMC, and the IRB.*
- ⊙ If subject had a positive STI result at Visit 2, the subject will be referred for treatment of that STI. The subject may proceed to Treatment Stage 1 (Visit 3) one week after a CDC-approved (Appendix X) treatment for the STI.
- ⊙ Update locator information and remind participant that he or she will receive visit reminders via email and/or telephone.
- ⊙ Collect copy of concomitant medication log
- ⊙ Review precautions listed in Section 5.1.1.

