### 5.3.2 Clinical Procedures

**NOTE: During this visit the timepoints listed below are approximate. Every effort will be made to adhere to the timeline, however due to logistics timing will not be exact. However, the sequence of sample collection during the following visits is crucial.**

- ⊙ Interval medical history\*, including AE assessment, will be collected to assure continued healthy status and safety of study interventions.
 

*\* Note for female participants this includes notation of the LMP.*
- ⊙ Basic physical examination as defined in section 5.1.2
 

*(If participant has peri-anal or rectal HSV lesions, referrals for treatment will be provided and Visit 3 will be postponed until outbreak resolved.)*
- ⊙ **If female of child-bearing potential, collect urine for STAT HCG testing**
- ⊙ Collect blood specimens, including pre-dose pK draw if applicable
- ⊙ Collect rectal swabs and sponge specimens

- ⊙ Administer preparatory Normosol-R pH7.4 enema
- ⊙ Collect stool specimen
- ⊙ T=0 Administration of single-dose of study gel by study staff  

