## 5.5 Visit 4- (Week 5 +/- 2 weeks) Treatment Stage 2 Clearance

### 5.5.1 Non-clinical Procedures

- If subject had a positive STI result at Visit 3, the subject will be referred for treatment of that STI. The subject may proceed to (Visit 4) one week after a CDC-approved (Appendix X) treatment for the STI.
- Update locator information and remind participant that he or she will receive visit reminders via email and/or telephone.
- Collect copy of concomitant medication log
- Review precautions listed in Section 5.1.1.
- At this time subjects will be given clearance, if applicable, to start the once daily rectal administration of study product the next day and reminded to complete Product Use Log during Treatment Stage 2.
- Give participant Product Use Log, with instructions for proper use.
- Dispense study product and lubricant with thorough instructions for proper use. Instruction will include self-insertion of an empty applicator while a staff member is available to provide guidance.

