## 5.6 Treatment Stage 2- Outpatient

### Up to 3 weeks after Visit 3:

- Subjects may not begin study product administration, until they have been given clearance by the staff pending clinical labs.  
*If any lab abnormalities  $\geq$  Grade 2 at Visit 3, subject may not proceed with Treatment Stage 2. If the investigator feels that the laboratory abnormalities are transient, the lab tests may be repeated within the visit window. If the repeated labs tests are within normal limits, the subject may proceed with Treatment Stage 2 at the discretion of the investigator, the DAIDS Medical Officer, the SMC, and the IRB.*
- On approximately Day 4 of Treatment Stage 2, an attempt to contact the subject for an interim follow-up phone-call to assess safety, adherence, and troubleshoot any difficulties with administration will be made. Potential AEs that arise may require further clinical evaluation. At this time subjects will also be reminded to complete Product Use Log.

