### 6.2 Adverse Event Evaluation Criteria

An AE is defined as any untoward medical occurrence in a clinical research participant administered an investigational product and which does not necessarily have a causal relationship with the investigational product.

All gastrointestinal AEs will be defined and graded as described in the 2006 DAIDS Rectal Toxicity Table Addendum (Appendix IV). Any AEs not defined in the DAIDS Rectal Toxicity Table will be defined and graded as described in the DAIDS Toxicity Table (Appendix V). The DAIDS Toxicity Table can be found in Appendix V and on-line at <http://rcc.tech-res-intl.com/>.

Each adverse event not described above or in the DAIDS Toxicity Table should be graded for severity using the following scale:

- ⊙ Mild: subject was aware of the adverse event, but she/he was still able to do all activities; no or minimal medical intervention/therapy required.
- ⊙ Moderate: the subject had to discontinue some activities due to the adverse event; no or minimal medical intervention/therapy required.
- ⊙ Severe: the subject was incapacitated by the adverse event and unable to perform normal activities; significant medical intervention/therapy required, hospitalization possible.

For pre-existing lab abnormalities and conditions, only changes  $\geq$  one Grade level will be reported as adverse events.

It is the responsibility of the investigator to determine if an adverse event is definitely related, possible related, probably related or, unrelated to the subject's participation the

study. The investigator or designee will assess the relationship of all AEs to the study product based on the DAIDS EAE Reporting Manual, the Investigator's Brochure, and his/her clinical judgment.

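### Section 6.1's Grade 3 trigger suspends accrual and convenes the SMC but does not hold new dosing starts while the SMC considers whether dosing should continue

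*Protocol*

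**What the plan says.** Protocol Section 6.1 provides two routes to the SMC. One is the protocol team's judgement, with no number attached. The other is numeric: once two or more participants have an adverse event of Grade 3 or higher, "accrual will be suspended and the UCLA SMC will be convened". If the SMC thinks the events may justify halting the trial, it is unblinded. The section continues: "The SMC will then analyze the data in an unblinded fashion and make the determination on whether to continue accrual and product use".

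The trigger is not limited by cause or arm. Section 6.2 defines an adverse event as one that "does not necessarily have a causal relationship with the investigational product".

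Dosing begins at two points, both controlled by staff:

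- **Stage 1 (Section 5.3.2, Visit 3):** "Administration of single-dose of study gel by study staff".
- **Stage 2 (Section 5.5.1, Visit 4):** "At this time subjects will be given clearance, if applicable, to start the once daily rectal administration of study product the next day". Section 5.6 adds: "Subjects may not begin study product administration, until they have been given clearance by the staff pending clinical labs".

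Randomization falls between enrollment at Visit 2 and the first dose. Section 2.2 says that after Visits 1 and 2 "eligible subjects will be randomized to one of three groups", and Section 5.3.1 reads "Randomize subject and assign participant ID number prior to Visit Day".

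**The concern.** Section 6.1 names accrual and product use as two separate matters for the SMC but pauses only the first while the SMC deliberates. If suspending accrual already stopped dosing, the separate mention of product use would be redundant. The automatic protection therefore covers people who have not yet joined. Enrolled participants can still start a dose or a seven-day course while the review is open.

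Section 8.3 expects minimal local irritation, but it also says that this formulation has not been given rectally to humans before and that the treatment risks are not known. A Stage 1 dose is followed about 30 minutes later by sigmoidoscopy with 28 biopsies (Section 5.3.2). Section 8.3 says the gel's unknown effect on the mucosa may raise the risk of biopsy complications. Stage 2 is seven self-administered daily doses with one attempted call around Day 4 (Sections 4.4 and 5.6). At stake is whether a few people begin that exposure during the review that is meant to decide whether anyone should.

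**Working it through.** **Does any other provision supply the hold?**

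| Provision | Acts on | Required by the 6.1 trigger? |
|---|---|---|
| Grade 2 or higher lab rule, STI, HSV and HCG checks (5.2, 5.3, 5.5, 5.6) | that participant's own results | No |
| Staff clearance for Stage 2 (5.5.1, 5.6) | that participant, pending clinical labs | No |
| Investigator withdrawal (3.5) | one participant, by judgement | No |
| Ad hoc team calls, convened SMC (6.1) | whole study, by judgement | SMC convened; no hold named |
| Telephone report of serious, possibly drug-associated events to CONRAD and DAIDS (6.4.2) | reporting | No |
| Discontinuation by NIAID, the IRB or agencies (8.8) | whole study, by judgement | No |

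No row requires dosing to wait. The SSP manual (Section 10.2) may add instructions, but it is not shown and Section 6.1 does not refer to it.

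**What does suspending accrual stop?** The protocol does not define accrual. There are two readings:

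- Reading A: it also stops randomization. Only Stage 2 starts continue.
- Reading B: it stops only Visit 2 enrollment. Stage 1 doses for people already past Visit 2 continue as well.

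**How many starts?** The protocol gives no figure, so this is an estimate. Inputs: 36 participants, two of three arms active, accrual over 9 to 12 months (Section 5.0). Assumptions: even accrual, and a review of 1 to 2 weeks, since the protocol states no duration.

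- Accrual rate: 36/52 = 0.692 per week (12 months) to 36/39 = 0.923 per week (9 months).
- Reading A, rate × weeks: 0.692 × 1 = 0.69 to 0.923 × 2 = 1.85 starts. On active gel (× 2/3): 0.46 to 1.23.
- Reading B, 2 × rate × weeks: 2 × 0.692 × 1 = 1.38 to 2 × 0.923 × 2 = 3.69 starts. On active gel: 0.92 to 2.46. This rate should not be carried beyond 2 weeks: Visit 3 nominally follows Visit 2 by 2 weeks, so Stage 1 doses then run out.
- Already inside the 7-day course at a given moment: rate × 1 week = 0.69 to 0.92, of whom 0.46 to 0.62 are on active gel.

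**How likely is the trigger?** For assumed true per-participant rates of Grade 3 or higher events, P(at least 2 of 36) = 1 − (1−p)^36 − 36p(1−p)^35. This is 0.050 at p = 1%, 0.543 at 5% and 0.887 at 10%. Because the rule counts events of any cause, it could be met without product toxicity.

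**After accrual closes.** The last participants still have Visit 3 (nominal Week 2) through Visit 5 (nominal Week 6) ahead, about 4 weeks. Suspending accrual then affects only replacements for people who leave before any dose (Section 3.5).

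**The case against.** The strongest reply is that Section 6.1 describes a coherent graded response. With a trigger this broad, in a trial with three sigmoidoscopies of 28 biopsies each, leaving current dosing to a convened SMC is defensible. A reader might infer that enrolled participants are left to one investigator's discretion. The documents do not support that: the trigger itself convenes the SMC, the team can hold ad hoc calls, serious drug-associated events are telephoned to CONRAD and DAIDS, outside bodies can stop the study, and participants have a 24-hour number (Section 6.3). That part of the reply stands. What remains is that none of these requires new starts to wait.

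A reader might also infer that the protocol plainly permits Stage 1 dosing during the review. That holds only on Reading B; on Reading A the gap is confined to Stage 2. Those participants have already had one dose, a 7-day recovery, a lab check and staff clearance.

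The background data are also fairly reassuring. A 1.0% gel, four times the highest strength here, was given rectally to macaques without a significant difference in epithelial sheets (Section 1.2.2.6). Women using 0.1% or 0.25% vaginally had no detectable plasma drug (Section 1.2.3). This lowers the expected risk, but Section 8.3 still calls the risks of treatment unknown.

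Finally, a hold affects the schedule. Section 5.6 allows Stage 2 up to 3 weeks after Visit 3, and nominal timing (Week 2 to Week 5) already uses all of that. A hold without an extension could cost participants their Stage 2 course, and dosed withdrawals are not replaced (Section 3.5). This objection is sound, and the amendment has to deal with it.

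**Conclusion.** The gap is real but limited, and should be closed. Section 6.1's only numeric study-level trigger has no consequence for new dosing starts while the SMC decides on product use, and no other provision requires one. Stage 2 starts are affected on either reading of accrual; Stage 1 doses only if accrual means Visit 2 enrollment.

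The size is about 0.7 to 1.8 new starts if randomization also stops and 1.4 to 3.7 if it does not, of which two thirds would be on active gel. These figures rest on even accrual and an assumed 1 to 2 week review. The wording conclusion rests on neither. The protocol does not direct that dosing continue, and staff could stop it by judgement; the fault is that the rule does not make them. Confidence is medium because the SSP manual is not shown.

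**What to change.** Amend Section 6.1 so that, when the trigger is met, accrual, randomization, new Stage 1 doses and new Stage 2 starts are suspended until the SMC reports, including after accrual is complete. Cross-refer to this in Sections 5.3, 5.5 and 5.6.

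For a participant already in the 7-day course, have the investigator and the SMC medical monitor (the role in Section 7.3.1) decide promptly whether to hold. An automatic stop is not proposed here: missed doses are not replaced (Section 4.6.1), each arm has only 12 participants, and the events may be unrelated to the gel.

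State in Sections 4.4 and 5.6 that the 3-week limit and the visit windows may be extended by the length of the hold, with clearance labs and HCG repeated if needed. State in Section 4.6.1 that doses held for this reason are not non-adherence; its present exception covers a participant who discontinues because of an adverse event, not a study-level hold.

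The cost is a few sentences, using the existing SMC, medical monitor and clearance step. Because the trigger counts events of any cause in any arm, some starts will be delayed for unrelated or placebo-arm events, and the interval between stages will be longer for a few participants.

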### 6.2 Adverse Event Evaluation Criteria

An AE is defined as any untoward medical occurrence in a clinical research participant administered an investigational product and which does not necessarily have a causal relationship with the investigational product.

All gastrointestinal AEs will be defined and graded as described in the 2006 DAIDS Rectal Toxicity Table Addendum (Appendix IV). Any AEs not defined in the DAIDS Rectal Toxicity Table will be defined and graded as described in the DAIDS Toxicity Table (Appendix V). The DAIDS Toxicity Table can be found in Appendix V and on-line at <http://rcc.tech-res-intl.com/>.

Each adverse event not described above or in the DAIDS Toxicity Table should be graded for severity using the following scale:

- ⊙ Mild: subject was aware of the adverse event, but she/he was still able to do all activities; no or minimal medical intervention/therapy required.
- ⊙ Moderate: the subject had to discontinue some activities due to the adverse event; no or minimal medical intervention/therapy required.
- ⊙ Severe: the subject was incapacitated by the adverse event and unable to perform normal activities; significant medical intervention/therapy required, hospitalization possible.

For pre-existing lab abnormalities and conditions, only changes  $\geq$  one Grade level will be reported as adverse events.

It is the responsibility of the investigator to determine if an adverse event is definitely related, possible related, probably related or, unrelated to the subject's participation the

study. The investigator or designee will assess the relationship of all AEs to the study product based on the DAIDS EAE Reporting Manual, the Investigator's Brochure, and his/her clinical judgment.

**“Suspected Adverse Drug Reaction” (SADR) means:**

An adverse event that could potentially have a causal relationship to a study agent (definitely, probably, possibly, probably not related or for deaths, pending).

**“Unexpected adverse drug experience” means:**

Any adverse drug experience in which the specificity or severity is not consistent with the current investigator brochure.

Definitions of relatedness:

- Definitely-** Adverse event and administration of study agent are related in time and a direct association can be demonstrated with the study agent.
- Probably-** Adverse event and administration of study agent are reasonably related in time and the adverse event is more likely explained by the study agent than other causes.
- Possibly-** Adverse event and administration of study agent are reasonably related in time and the adverse event can be explained equally well by causes other than the study agent.
- Probably not-** Potential relationship between the study agent and adverse event could exist, but is unlikely, **and** the adverse event is most likely explained by causes other than the study agent.
- Not related-** The adverse event is clearly explained by another cause not related to the study agent (must have documentation to support this determination).

### 6.3 Adverse Experience Reporting Requirements

Study participants will be provided with a list of danger signs and a 24-hour telephone number. Participants will be instructed to contact the study clinician to report not only danger signs, but also any events they may experience, except for life-threatening events, for which they will be instructed to seek immediate emergency care. Depending on the severity of the event, the clinician will instruct the participant to present to the study site (for more mild events) or to an emergency room (for more serious events) for immediate evaluation. Where feasible and medically appropriate, participants will be encouraged to seek medical care where the study clinician is based, and to request that the clinician be paged or otherwise contacted upon their arrival. With appropriate permission of the participant, records from all non-study medical providers related to such events will be obtained and required data elements will be filed with the source documentation. All participants reporting an AE will be followed clinically, until the AE resolves (returns to baseline), stabilizes or their last study visit. Subjects may be followed for longer periods of time per the discretion of the investigator, DAIDS, and the sponsor.

#### Pregnancy

*Pregnancy will not be considered an Adverse Event for this study. Pregnancy will require the subject to be withdrawn from the study. However, in the event that a subject becomes pregnant during the study every reasonable effort will be made to follow her through pregnancy outcome. Consent for the site to receive a copy of her medical records related to the pregnancy should be obtained.*

*Anytime a live birth pregnancy is reported, an attempt to collect medical records of the neonate should be made.*

Study site staff will document on study CRFs all AEs reported by or observed in enrolled study participants regardless of severity and presumed relationship to the study product and procedures.

Information on all AEs will be included in reports to the US Food and Drug Administration (FDA), and other applicable government and regulatory authorities. Site staff will report information on all AEs and EAEs to their Institutional Review Board (IRB) in accordance with all applicable regulations and local IRB requirements.

